### Data Analysis

Hypotheses will be tested using R software. All analyses will initially be performed as intention-to-treat, and per-protocol analyses will also be undertaken for comparison. Patterns of missing data will be explored using the Little missing completely at random test. Missing data in the final analysis will be inferred using full-information maximum likelihood analysis. We will test the efficacy of the intervention on our primary outcome, self-reported leisure-time physical activity, using an iterative series of generalized linear models. Independent variables will include time, intervention condition, demographic covariates (eg, start date, gender, and age), delivery group clustering, within-dyad clustering, and person-intervention theory fit *P*Δ [51]. Each variable group will be added in a subsequent iteration of the model, and model fit statistics will be examined at each iteration. This process will be repeated for each secondary outcome variable (perceived autonomy support, autonomous motivation, attitude, subjective norm, perceived behavioral control, action planning, coping planning, self-monitoring, and behavioral automaticity).

We also intend to assess the effect of theory-based mediators on change in physical activity using a path model. Specifically, we aim to assess whether the effects of intervention conditions on change scores in physical activity outcomes (both primary and secondary) are mediated by change scores in each of the psychological constructs targeted by the intervention (ie, perceived autonomy support, autonomous motivation, attitude, subjective norm, perceived behavioral control, action planning, coping planning, self-monitoring, and behavioral automaticity).

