## Methods

### Trial Design

The trial will adopt a randomized waitlist control design in which parent-child dyads are the unit of randomization. Families will be randomized on sign-up to either an intervention group that receives the intervention immediately after baseline data collection or to a waitlist control group that will receive the intervention after all outcome data have been collected.

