### Power Analysis

The projected sample size was estimated from a statistical power analysis conducted using G*Power (version 3.1; Heinrich-Heine-Universität Düsseldorf). The analysis assumed a small to medium effect size (Cohen *f*=0.235) for the intervention on our primary outcome variable, leisure time physical activity, calculated from an average of effect sizes from meta-analyses of self-determination theory–based interventions (Hedges *g*=0.45 [35]) and interventions targeting self-efficacy (Cohen *d*=0.48 [36]), with α set at .05 and statistical power set at .80 reveal a projected total sample size of 178 participants. We also assumed a projected 30% attrition rate in participants through the study based on similar trials [37], resulting in a sample of 254 participants (ie, 127 dyads) to be recruited at baseline.

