#### Primary Outcomes (Physical Activity and Sedentary Time)

Self-reported physical activity and time spent in sedentary activities for both parents and children will be assessed using the Godin-Shepard leisure time exercise questionnaire [41], where participants will be required to report the number of occasions they engaged in light, moderate, and vigorous physical activity for 15 minutes or longer. Sedentary time will be measured using 2 items per participant, targeting weekdays and weekend days separately (eg, “In the past 7 days, how much time did you spend sitting during a typical weekday after school or weekend day?”) [42]. Items are scored on a sliding scale from “no time” upwards in increments of half an hour.

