##### Subjective Norms

Subjective norms in parents are assessed using 3 items referring to important others [44,47]. Children answered similar items, but in specific reference to family and friends separately. All items are scored on a 5-point Likert scale (1=strongly disagree to 5=strongly agree).

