## Discussion

### Overview

This protocol presents a randomized controlled trial aiming to increase physical activity levels in inactive parent-child dyads within Finland, based on the integrated behavior change model. We hypothesize in this protocol that both parents and children will show increased levels of physical activity, our primary outcome variable, both at the immediate and 3-month postintervention stage, relative to a waitlist control group. Further, we hypothesize we will observe similar changes in the trial’s secondary outcomes, the psychological constructs of the integrated behavior change model (ie, autonomy support, autonomous motivation, attitude, subjective norm, perceived behavioral control, self-monitoring, intentions, and habit), in the intervention group relative to the waitlist control group.

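### The primary model as listed has no parent/child term, so its condition effect is an average over roles and does not by itself test the hypothesis that both parents and children become more active

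*Protocol article*

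**What the plan says.** The Overview of the Discussion states the hypothesis for the primary outcome by role: "both parents and children will show increased levels of physical activity, our primary outcome variable, both at the immediate and 3-month postintervention stage", relative to the waitlist group.

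The Data Analysis section describes one analysis of that outcome: "We will test the efficacy of the intervention on our primary outcome, self-reported leisure-time physical activity, using an iterative series of generalized linear models". The terms are given as "Independent variables will include time, intervention condition, demographic covariates (eg, start date, gender, and age), delivery group clustering, within-dyad clustering, and person-intervention theory fit". No role factor, no condition-by-role interaction and no separate parent and child models are named. For the other outcomes, "This process will be repeated for each secondary outcome variable".

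The outcome is measured in each role with the same instrument: "Self-reported physical activity and time spent in sedentary activities for both parents and children will be assessed using the Godin-Shepard leisure time exercise questionnaire". Under Trial Design, "parent-child dyads are the unit of randomization". The Power Analysis section works in individuals: 178 evaluable and 254 recruited, the latter equated with 127 dyads. It does not split the number or the effect size by role.

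Some secondary measures differ between roles. For subjective norms, parents rate important others, while "Children answered similar items, but in specific reference to family and friends separately". Perceived autonomy support refers to the family when parents answer and to the parents when children answer.

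**The concern.** A claim about both roles fails if either role does not improve. A single condition coefficient fitted to parents and children together answers a different question: whether the mean effect over the two roles differs from zero. It can be significant when only one role has responded.

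The age covariate does not repair this. Eligible children are 8 to 12 and parents are over 18, so age nearly identifies role, but as a main effect it shifts the level of activity and leaves the intervention effect common to both roles.

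At stake is the wording of the main conclusion. The Introduction gives the decline in children's activity as a principal reason for the trial, and the Discussion treats parents and children as separate target populations. A significant pooled coefficient could be reported as a benefit to both without evidence for each. The ambiguity also reaches the stopping rule under Study Procedures, where collection of 6-month data depends on one effect that is not defined by role.

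**Working it through.** **Inputs from the protocol article.** Cohen f = 0.235, which for two equal groups is d = 2 × 0.235 = 0.47; alpha 0.05; power 0.80; 178 evaluable individuals, so 178/2 = 89 dyads; 30% attrition.

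**Assumptions not in the article.** Equal allocation (44.5 dyads per arm), two-sided test, unit-variance outcome, dyads handled correctly, and within-dyad correlation r from 0.1 to 0.5. The split of effects by role is also assumed.

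**The plan's own figure.** With noncentrality f² × N, f = 0.235 and numerator df = 2, N = 178 gives power 0.801, so 178 reproduces. For attrition, 178/0.7 = 254.3, against 254 stated. The point here does not depend on this figure being right or wrong; it matters only that it counts both roles together.

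**Standard errors.**
- One role: SE = √(2/44.5) = 0.212.
- Average over roles: SE = 0.212 × √((1 + r)/2), which is 0.157, 0.171 and 0.184 for r = 0.1, 0.3 and 0.5.

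**Scenario A: parents 0.47, children 0.** The average effect is 0.47/2 = 0.235. The chance of a significant result in favour of the intervention is Φ(effect/SE − 1.96).

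| r | pooled: effect/SE | pooled, formula | pooled, simulation |
|---|---|---|---|
| 0.1 | 1.49 | 32% | 31.7% |
| 0.3 | 1.37 | 28% | 27.2% |
| 0.5 | 1.28 | 25% | 24.4% |

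The simulation used 40,000 trials per scenario, 44 versus 45 dyads, and a t-test on the dyad mean. A parent-specific test has 0.47/0.212 = 2.22 and Φ(0.26) = 60% power (simulation about 59%). Both roles are significant together in about 2% of these trials.

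**Scenario B: 0.47 in both roles.** Simulated power for r = 0.1, 0.3 and 0.5:
- pooled test: 84%, 78%, 72%
- each role separately: about 60% (formula)
- both roles significant: 37%, 40%, 44%

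Scenario A shows how far the pooled answer can differ from the role-specific one. Scenario B shows what role-specific reporting costs in precision.

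**The case against.** The strongest reply is that the list in Data Analysis is shorthand and not a model formula. It names no interaction at all, not even condition by time, and its demographic examples are open-ended, so silence on role is not proof of exclusion. A within-dyad term shows that both members are modelled jointly, but a joint model can still carry separate effects. This stands to the extent that pooling is inferred and not stated. It does not remove the point, because nothing in the article names a term or a separate model that would yield role-specific effects.

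Three stronger readings are tempting, and the document does not support them.

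- A reader might set the 24% to 32% against a nominal 2.5% and call the excess false positives. It is not: in Scenario A the true average effect is 0.235 SD, so the pooled null is false and rejecting it is correct. The error would lie in wording the result as a benefit to both roles.
- A reader might infer from the parents-only first session and the parents' chat group that only parents will respond. That session teaches autonomy-supportive parenting, which the Introduction presents as a route to children's activity, and the other three sessions include children. The zero child effect is an assumption.
- A reader might conclude that the trial cannot tell whether children benefited. Parents and children have separate surveys, so role-specific estimates remain available.

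It is also fair to say that the abstract's objective, efficacy among parent-child dyads, can be answered by an average effect, and that the article sets no rule requiring significance in each role.

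**Conclusion.** The point holds as a mismatch between the stated hypothesis and the model listed to test it. The hypothesis concerns both roles; the model, followed as written, gives one effect averaged over them. Under the assumptions above, a parent-only effect of 0.47 SD would make the pooled test significant in about a quarter to a third of trials with no change in children, while about half of the power of a parent-specific test (59%) would be lost. The size depends on the assumed zero child effect and on the within-dyad correlation, neither of which the article gives. The mismatch itself does not depend on them.

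It does not follow that the average effect is an invalid target, or that the trial must require significance in both roles to succeed. With 37% to 44% power for both at the planned effect, such a rule would more often fail than succeed even if the intervention worked as assumed in each role.

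**What to change.** In the Data Analysis section, add role (parent or child) and its interaction with condition and time to the primary model. Report the intervention effect with a confidence interval for parents and for children from that joint dyadic model. Keep the pooled estimate, labelled as an average over roles. State that any claim about both parents and children will be worded only from the role-specific results. For outcomes whose items or referents differ by role (subjective norms, perceived autonomy support), report role-specific effects. Say also in which role, or on which average, the stopping rule judges that there is no effect.

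The cost is a few model terms and some wording; no further data or participants are needed for the reporting. The drawback should be stated openly: at 0.47 SD and 89 dyads, power is about 60% per role and 37% to 44% for both, against 72% to 84% for the pooled average. If the sponsor wished to power the both-roles claim at 80%, it would need about 178 to 188 evaluable dyads (r from 0.5 down to 0), which is about 255 to 269 recruited at 30% attrition, against 127 planned. That is a separate decision and is not required by this change.

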**Results:**

This study will reveal whether the intervention changes leisure-time physical activity among intervention participants relative to the control group and will examine the intervention’s effects on important theoretical predictors of physical activity. It will also yield data that can be used to refine intervention materials and inform further implementation. Trial recruitment commenced in September 2023, and data collection should be completed by December 2024.

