### Study Procedures

All recruitment materials will be delivered in a web-based format with a URL forwarding participants to a screening and informed consent survey hosted on the Webropol platform. First, parents will be presented with an eligibility questionnaire to assess whether they and their children making reference to themselves and their least active child aged between 8 and 12 years, meet the inclusion criteria. Eligible parents will then be presented with information about the study and an informed consent form. Parents who provide informed consent to participate in the study will be prompted to provide their name, contact details, and the name of their least active child, aged between 8 and 12 years, and will be enrolled in the study.

After enrolling in the trial, dyads will be assigned by computerized random-digit generation to 1 of 2 groups: an immediate intervention group that receives the intervention immediately after baseline data collection, or a waitlist control group that will receive the intervention after all outcome data have been collected.

Participants in both groups will be asked to provide outcome data immediately after randomization, 3 months later, and 6 months later. Outcome data will be collected through web-based surveys hosted on the Webropol platform and through physical activity measurement devices mailed to participants’ homes. For web-based surveys, parents will be emailed 2 separate URLs: 1 for themselves and 1 for their child. Parents will be instructed that they may help their child understand the survey items but should avoid influencing their child’s answers to the questionnaire.

Participants in the immediate intervention group will receive the intervention between the baseline and 3-month data collection points, while participants in the waitlist control group will receive the intervention after all data collection has been completed. While data are planned to be collected at baseline, 3 months, and 6 months, the trial includes a stopping rule, such that 6-month follow-up data will not be collected if there is no effect of the intervention on the primary outcome (ie, leisure time physical activity) at the 3-month follow-up. The trial design flow diagram is presented in Figure 1.

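### The primary model names time and condition but neither a condition-by-time term nor baseline activity; fitted as listed, its condition coefficient would be attenuated, most of all at the 3-month stopping decision

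*Protocol article*

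**What the plan says.** The Data Analysis section tests the primary outcome, self-reported leisure-time physical activity, "using an iterative series of generalized linear models". The terms are given as a list: "Independent variables will include time, intervention condition, demographic covariates (eg, start date, gender, and age", followed by clustering by delivery group and by dyad and a measure of person-intervention theory fit. On model building it says "Each variable group will be added in a subsequent iteration of the model, and model fit statistics will be examined at each iteration". Neither sentence names an interaction of condition with time, and baseline physical activity is not among the covariates given as examples.

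Study Procedures sets three waves: "Participants in both groups will be asked to provide outcome data immediately after randomization, 3 months later, and 6 months later". The first precedes treatment: "Participants in the immediate intervention group will receive the intervention between the baseline and 3-month data collection points". The same section makes the last wave depend on the 3-month result: "6-month follow-up data will not be collected if there is no effect of the intervention on the primary outcome" at that point.

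The Discussion (Overview) hypothesises higher activity than in the control group both straight after the intervention and 3 months after it. The Abstract (Results) describes the aim as learning "whether the intervention changes leisure-time physical activity among intervention participants relative to the control group".

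**The concern.** Because time is a predictor, the outcome is modelled over several waves. If baseline is one of them and condition enters only as a main effect, the model assumes the same arm difference at every wave, including the one before anyone is treated. Randomisation makes that difference zero in expectation, so the coefficient is pulled toward zero, and any chance imbalance at baseline feeds into it.

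Such a model also cannot give separate 3-month and 6-month differences, which the hypothesis requires. The stopping decision is the most exposed use. Only two waves exist then, so the untreated wave carries half the weight, and a diluted estimate could lead to the 6-month data not being collected for an intervention that works.

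**Working it through.** **Inputs.** From Power Analysis: effect sizes 0.45 and 0.48, f = 0.235, alpha 0.05, power 0.80, N = 178, 30% attrition, 254 recruited. From Study Procedures: three waves, the first before treatment. The correlations, the timing of dropout and the course of the effect are not in the article and are assumed below.

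**The plan's own figure.**
- Mean effect: (0.45 + 0.48)/2 = 0.465 SD. For two equal arms f = d/2 = 0.2325, which the plan gives as 0.235.
- Noncentral F with f = 0.235, alpha 0.05 and power 0.80 gives N = 145 with numerator df 1, **178** with df 2, and 202 with df 3.
- Attrition: 178/0.70 = 254.3, stated as 254.
- A condition main effect in two arms has df 1. A 2-arm by 3-wave interaction has (2−1)(3−1) = 2, but so does a comparison of three groups. The 178 is therefore compatible with an intended interaction without proving it.

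**Expected condition coefficient in outcome ~ time + condition.** Let δ be the 3-month effect, with baseline as an outcome row and an identity link. With complete data and an exchangeable correlation, the coefficient is the plain mean of the wave-specific differences, whatever the correlation.
- Three waves, equal effect at 3 and 6 months: (0 + δ + δ)/3 = 0.667δ, that is 0.31 SD for δ = 0.465.
- Effect halved by 6 months: (0 + δ + 0.5δ)/3 = 0.50δ.
- Effect gone by 6 months: (0 + δ + 0)/3 = 0.33δ.
- Two waves, as at the stopping decision: (0 + δ)/2 = 0.50δ, that is 0.23 SD.

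**With attrition.** Full-information maximum likelihood keeps the baseline rows of participants who drop out, so baseline gains weight. At zero correlation the weights are the retained fractions. The second figure in each line is at within-person correlation 0.7.
- Retention 100/85/70%, equal effect: (0.85 + 0.70)/2.55 = 0.61, falling to 0.56.
- Retention 100/70/70%, equal effect: (0.70 + 0.70)/2.40 = 0.58, falling to 0.50.
- Two waves with 30% lost by 3 months: 0.70/1.70 = 0.41, falling to 0.37.

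**Illustrative power.** 178/4 = 44.5, so take 44 dyads per arm. Assume within-person correlation 0.6, parent-child correlation 0.3 and δ = 0.465. A dyad mean at one wave has variance (1 + 0.3)/2 = 0.65. For a test whose dyad-level variance is v, SE = √(2v/44). Power is two-sided from the noncentral t on 86 df.

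| Test | v | SE | Expected estimate | Power |
|---|---|---|---|---|
| Main effect, three waves | 0.65 × (1 + 2×0.6)/3 = 0.477 | 0.147 | 0.310 | 0.55 |
| Main effect, two waves | 0.65 × (1 + 0.6)/2 = 0.520 | 0.154 | 0.2325 | 0.32 |
| 3-month condition-by-time contrast | 0.65 × 2(1 − 0.6) = 0.520 | 0.154 | 0.465 | 0.85 |
| 3-month difference, baseline as covariate | 0.65 × (1 − 0.6²) = 0.416 | 0.138 | 0.465 | 0.92 |

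Setting 0.55 against 0.92 mixes two things, attenuation and baseline adjustment. The second and third rows separate them. At this correlation their standard errors are equal, so the difference between 0.32 and 0.85 comes entirely from halving the estimate.

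**The case against.** The strongest reply is that the article gives a list of variables, not a model formula. The list is open, and it includes clustering terms that would ordinarily enter as random effects or a covariance structure, so it cannot be a literal list of fixed main effects. Nowhere is the condition coefficient named as the effect estimate, and nowhere is baseline said to be an outcome row. The hypothesis, the stopping rule and the change scores in the mediation model all point to wave-specific or change contrasts, and 178 does not arise from a one-degree-of-freedom test. A condensed article may also leave the exact formula to an analysis plan.

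Much of this stands. A reader might infer that the trial has committed itself to an estimate that is a third too small. The documents do not support that: the estimate is not named, and the one-third figure needs complete data, an equal effect at both follow-ups and an identity link, whereas the plan projects 30% attrition and states no link. The power figures rest on assumed correlations. The change-score path model is not affected.

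What does not stand is that the interaction can simply be taken as read. The section goes as far as naming start date and theory fit and describes how terms are added in turn, yet omits the one term that carries the primary hypothesis. An open list also leaves the choice between a main effect, an overall interaction test and a single-wave contrast to be made after the data are seen.

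**Conclusion.** The point holds as a mismatch within the article: the listed model terms do not deliver the effects that the hypothesis and the stopping rule call for. If the model is fitted as listed, with baseline as a level of time and an identity link, the condition coefficient recovers 0.67 of the effect in the most favourable case examined (three complete waves, sustained effect). It recovers 0.50 to 0.61 under the two 30% attrition patterns tried, and 0.33 to 0.50 of the 3-month effect if the effect fades. At the stopping decision it recovers 0.50 with complete data and about 0.37 to 0.41 with 30% lost by then. If a condition-by-time model was intended, none of this attenuation arises and one sentence settles the matter. The documents do not show which was meant, so it cannot be said that the reported effect will be understated, or by a fixed third.

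**What to change.** State in Data Analysis that the primary estimate is the condition contrast at 3 months, adjusted for baseline physical activity. Either of two forms will do:
- the baseline score as a covariate, with the 3- and 6-month values as outcomes and condition allowed to differ by wave; or
- one longitudinal model of all three waves with condition-by-time terms and the baseline mean constrained equal between arms.

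Name that 3-month contrast as the input to the stopping rule, make the 6-month contrast secondary, and say that the condition main effect over all waves is not an efficacy test. Whether the effect is also allowed to differ between parents and children is a separate, optional choice.

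The cost is a few sentences of analysis text. No new data are needed, since baseline is already collected. The wording should be settled before the arms are compared at 3 months.

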#### Waitlist Control Group

Participants assigned to the waitlist control group will complete the same data collection procedures as the immediate intervention group but will not be required to undertake any alternative intervention tasks during the data collection period. After the data collection period, participants in the waitlist control group will be invited to receive the intervention and accompanying materials.

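### The primary analysis is a stepwise model series in which the unit of randomisation enters late and no iteration is fixed as the confirmatory test

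*Protocol article*

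**What the plan says.** Trial Design states that "parent-child dyads are the unit of randomization". Under Study Procedures, "Participants in both groups will be asked to provide outcome data immediately after randomization, 3 months later, and 6 months later", so a completing dyad supplies up to six rows of data. The same section makes collection of the 6-month data conditional on an effect on the primary outcome at 3 months.

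Data Analysis tests the primary outcome "using an iterative series of generalized linear models". The terms are listed in one sentence: "Independent variables will include time, intervention condition, demographic covariates (eg, start date, gender, and age), delivery group clustering, within-dyad clustering", with a measure of person-intervention theory fit last. The building rule follows: "Each variable group will be added in a subsequent iteration of the model, and model fit statistics will be examined at each iteration". The same process is then applied to each secondary outcome.

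The section also says: "Missing data in the final analysis will be inferred using full-information maximum likelihood analysis". It does not say which iteration that final analysis is. It lists time and condition but names no condition-by-time term.

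**The concern.** When dyads are randomised, two people share each allocation. A test of the arm effect that leaves the dyad out is therefore not a valid test of this design, whatever its fit. The stated procedure nevertheless places "delivery group clustering, within-dyad clustering, and person-intervention theory fit" after condition, time and demographics, as blocks that come in later and are checked by fit like any covariate. Followed as written, it produces several estimates of the treatment effect, and at least the first ones ignore the unit of randomisation.

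Since no iteration is named as confirmatory, two things are open: which p-value answers the primary question, and which one triggers the stopping rule at 3 months. The tested contrast is also open. That matters because ignoring correlation has opposite effects on an arm main effect and on an arm-by-time term.

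**Working it through.** **Inputs.** From the protocol: dyads randomised (Trial Design), three waves (Study Procedures), 178 persons analysed and 254 recruited (Power Analysis). The plan's own figure reproduces as a noncentral F test on independent persons with f = 0.235, α = 0.05 and 2 numerator degrees of freedom: power is 0.801 at N = 178, and 178/0.7 = 254.3. No allowance for dyads is needed to reach it. 178/2 = 89 dyads, and the simulations below used 88 (44 per arm). The document gives no correlations, so all of those below are assumptions.

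**Formula.** If all rows are treated as independent, the true variance of the arm difference is DE times the assumed one, where DE = 1 + the sum of a row's correlations with the other rows of its dyad. Type I error at a nominal 5% is then 2(1 − Φ(1.96/√DE)).

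**One wave per person, dyad ignored: DE = 1 + ρ.**

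| Dyad ρ | DE | Type I error |
|---|---|---|
| 0.1 | 1.1 | 6.2% |
| 0.2 | 1.2 | 7.4% |
| 0.3 | 1.3 | 8.6% |
| 0.4 | 1.4 | 9.8% |
| 0.5 | 1.5 | 11.0% |

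**Two post-baseline waves as independent rows, arm main effect.** With the same partner correlation within and across waves, DE = 1 + ρ(person) + 2ρ(dyad).

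| ρ(dyad) | ρ(person) | DE | Formula | Simulated |
|---|---|---|---|---|
| 0.1 | 0.5 | 1.7 | 13.3% | 13.6% |
| 0.2 | 0.5 | 1.9 | 15.5% | 15.5% |
| 0.2 | 0.7 | 2.1 | 17.6% | 17.4% |
| 0.3 | 0.6 | 2.2 | 18.6% | 18.5% |

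A dyad-level analysis of the same simulated data gave 4.7% to 5.2%.

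**Three waves as independent rows, arm main effect.** With ρ(person) = 0.6, ρ(dyad) = 0.3 and a cross-wave partner correlation of 0.6 × 0.3 = 0.18, DE = 1 + 2(0.6) + 0.3 + 2(0.18) = 2.86. Type I error is 24.6% (simulated: 24.7%). This is the upper end because it pools the baseline wave into the arm effect.

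**Arm-by-time, all rows independent.** Differencing removes what a person's waves share. In the two-wave structure above, the true variance is (1 − ρ(person)) times the assumed one, so type I error is 2(1 − Φ(1.96/√(1 − ρ))): 0.56% at 0.5, 0.19% at 0.6 and 0.03% at 0.7 (simulated: 0.7%, 0.15%, 0.025%). In the three-wave structure the factor is (1 − 0.6) + (0.3 − 0.18) = 0.52, giving 0.66% (simulated: 0.6%).

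**Dyad random intercept included, no person term** (ρ(dyad) 0.2, ρ(person) 0.5). A 300-run simulation gave 7.3% for the arm effect and 2.7% for arm-by-time. The Monte Carlo standard error at 5% is √(0.05 × 0.95/300) = 1.26 points, so 7.3% is only (7.3 − 5)/1.26 = 1.8 standard errors above nominal. With complete data the arm standard error rests on the between-dyad mean square, which does not need the person term; a 20,000-run check of that case gave 5.1%. Arm-by-time stays conservative. Over three waves the within-dyad variance that the model uses is (1 × 1.4 + 4 × 0.5)/5 = 0.68 against a true 0.5, and 2(1 − Φ(1.96 × √(0.68/0.5))) = 2.2%.

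**Clustering as literal independent variables.** Condition is constant within a dyad, so a full set of dyad indicators determines condition and its main effect cannot be estimated; condition-by-time still can. Delivery groups raise the same problem if only intervention dyads carry a group label. During data collection the controls "will not be required to undertake any alternative intervention tasks during the data collection period", which makes that likely but does not state it.

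**The case against.** The strongest reply is that both clustering levels are in the plan. A cumulative build ending in a model with dyad and delivery-group terms fits the wording, and the missing-data sentence mentions a final analysis. Clustering more naturally means random effects than indicator variables, and a condensed article may leave covariance structure to a fuller document.

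Much of this stands, and it rules out three stronger readings that a reader might infer:

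- That the confirmatory model is chosen after seeing the data. The text says fit is examined. It does not say that fit selects the model, or that clustering is dropped when fit does not improve.
- That the standard errors of the primary analysis are wrong. This is shown only for iterations without clustering terms. Once a dyad intercept is in, the arm effect is close to nominal in the balanced case.
- That the unnamed person-level term is an error. It may be specified in a fuller plan, and in the case checked its absence makes the change contrast conservative rather than producing false positives.

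Aliasing is likewise conditional on fixed-effect coding.

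The reply does not meet the main point. The article does set out a procedure. That procedure makes the randomisation unit a late block and names neither a confirmatory iteration nor a contrast, while a decision about trial conduct hangs on the 3-month result.

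**Conclusion.** The point holds in this form: the plan sets out a sequence of treatment-effect tests, the early ones ignore the unit of randomisation, and nothing fixes which one is the primary test or the trigger for the stopping rule.

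For iterations without clustering terms, type I error is about 6% to 11% with one wave per person. It is about 14% to 25% for an arm main effect with repeated waves as independent rows, and below 1% for arm-by-time. The ranges rest on assumed dyad correlations of 0.1 to 0.5 for one wave, and of 0.1 to 0.3 with within-person correlations of 0.5 to 0.7 for repeated waves. They do not describe a final model that contains the dyad term, and the documents do not show that an early iteration would be the one reported.

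**What to change.** In Data Analysis, name one confirmatory mixed model and one treatment contrast before outcome data are examined: the arm difference at 3 months, either baseline-adjusted or as arm-by-time. Include from the start random effects for dyad and for person within dyad, and a delivery-group effect in the intervention arm. State that these terms stay in whatever the fit statistics show. If the baseline-adjusted form uses the 3-month wave alone, each person supplies one outcome row and the person effect is not needed.

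State that this model, fitted to data up to 3 months, also gives the result used for the stopping rule in Study Procedures. Keep the iterative series, including the person-intervention fit measure, and label it exploratory.

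The cost is analysis wording and standard mixed-model code in R, with somewhat wider intervals for any between-arm main effect than the early iterations would give.
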